### Reasons for failure to be recruited

The proportion of patients who were missed, which should be minimal and proportion of patients who decline to take part will be recorded. Patients decline participation for many reasons, which should be captured whenever possible.

### Education material of nurses and surgeons

Feedback on the appropriateness, value and acceptability of the training will be elicited to enable refinement of the training programme for the substantive study, and to define a minimum competence. The training material will be evaluated for its ease of use, should it be used in the substantive study.

### Assessment of data collection process

Data will be collected using a CRF and will include demographic information and comorbidities. Postoperative complications will be defined by the European Society of Thoracic Surgery,^31^ Thoracic Morbidity and Mortality system^32^ and the stEP-COMPAC Group^33^ (see online supplemental appendix for definitions). Hospital readmission rate will be determined within 30 days of discharge.

Assessment and identification will be made for loss of data during in-hospital stay to improve the data collection process for the substantive trial.

### Smoking-related outcomes

In this study, the feasibility of the following questionnaires will be tested:

Self-reported quit rate and exhaled CO measurement.Fagerstrom Test for Nicotine Dependency: assessment of nicotine addiction.^34^
Mood and Physical Symptoms Scale: assessment of cigarette withdrawal symptoms over the past 24 hours, including the strength of urge to smoke.^35^
Generic health-related quality of life (EQ-5D-5L): assessment to provide a preference-based measure of health-related quality-of-life.^36^
NRT and support usage questionnaire.Health resource usage questionnaire: assessment of resource will be assessed via patient-recall with resources being measured including planned hospital overnight stays, planned hospital outpatient visits, hospital emergency visits, hospital admissions, GP and other community service visits.

### Acceptability to and impact on patients

All patients consenting to participate in the trial will be eligible for interview and selected using maximum variety sampling by age, sex, ethnicity, admitting diagnosis, surgical procedure and smoking status. Interviews will be conducted until saturation is achieved, which is likely to be around 25–30 patients across all sites.^37^ Telephone interviews will be conducted as to minimise impact to patients following major surgery, will last no longer than 60 min and will be audio recorded and transcribed by the researcher.

An interview guide will be developed using evidence from previous experience of running the rehabilitation and pain study, and based on the interview objectives: presurgical and postsurgical experiences of patients receiving the intervention (including effectiveness of staff communication) and patient engagement with it, any unintended consequences, acceptability of the intervention to patients and recommendations for how its use or content/design could be improved.

### Assessment of trial processes and impact on staff

Key HCPs in the clinical pathway will be invited to attend a focus group or individual interviews that will explore both the acceptability and recommendations for optimisation of the intervention (see online supplemental consent form: staff interviews).

10.1136/bmjopen-2019-036568.supp2Supplementary data

Digitally recorded interviews and focus groups will be transcribed verbatim and anonymised. Transcripts will be analysed for patients and staff separately following Braun and Clarke’s method for thematic analysis. Analysis will take an iterative approach, where data collection and analysis occurs concurrently, allowing the topic guide to be modified throughout to reflect emergent and/or priority themes.

## Statistics and data collection

### Sample size calculation

As this is a feasibility study, no formal sample size calculation has been performed. An audit discussing sample size in pilot and feasibility studies concluded that while sample size justification is important, formal calculation may not be appropriate. The findings from the audit concluded that a median size of 30 in each arm is appropriate.^38^ The study will aim to enrol 60 participants in the INT group over 1 year as this is a sufficient number to estimate a proportion of patients who have quit smoking by the day of surgery,^39^ as well as to explore data collection processes, and inform sample size calculations for a potential larger trial. Recruitment of 60 participants in each group will allow us to measure recruitment and compliance rates with 95% CI width between 10% and 20%. It would also be enough to estimate the SD of questionnaires with reasonable accuracy for future planning of a larger trial.

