### The need for integrated hospital-based smoking cessation support

The current National Institute of Health and Care Excellence (NICE) guidance is that smokers undergoing ‘elective’ surgery should receive behavioural support and stop-smoking pharmacotherapy as early as possible in their outpatient or preoperative assessments. This should be offered weekly, preferably face-to-face, for a minimum of 4 weeks after the quit date.^6^ The Cochrane review supporting this type of ‘intensive’ intervention^7^ was based on two small trials in orthopaedics and general surgery.^8 9^

However, in current practice, most thoracic surgery patients do not receive any preoperative smoking cessation support. Of the 120 patients attending a large UK thoracic regional unit, only 40% of current smokers were offered support,^10^ similar to the proportion of all eligible preoperative patients agreeing to participate in smoking cessation studies.^11 12^ Only one in three smokers self-report abstinence at the time of lung cancer surgery,^4^ with biochemical verification indicating much lower quit rates.^7^

Thus, the current usual care (UC) of referral to stop-smoking services does not meet the standard set by NICE. This may be due to these services being designed to promote long-term quitting, which many smokers undergoing surgery may not be willing to commit to. Many patients also report that attending smoking cessation clinic appointments during their work-up for surgery is a significant barrier to stopping smoking and would prefer bespoke support during hospital visits.^13^

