### Primary objective

To establish the number of patients who agree to participate in the intervention as a proportion of those eligible to enter the study.

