## Outcome and data collection

### Patient recruitment into study

The overall aims of the feasibility are to find out if a larger trial is feasible. The quantitative measurements related to this include the following:

Proportion of all elective thoracic procedures screened.Proportion of eligible participants of those screened.Proportion of eligible participants consented to receive intervention.

In this feasibility study, selecting five units whose overall elective thoracic patient throughput amounts to 4000 patients a year, of whom 20% are smokers and 20% agree to take part in the study. It is expected that 60 eligible patients will be recruited to the INT group and 60 patients to the UC group of the study, with recruitment of 120 patients in total. Therefore, the aim is to recruit five patients a month to each group over the 12 months recruitment period across all sites.

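### The 95% CI width of 10% to 20% stated for 60 per group fails for mid-range rates, and recruitment precision depends on the number eligible, not on 60

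*Protocol article*

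**What the plan says.** Under Sample size calculation, the protocol article says that "As this is a feasibility study, no formal sample size calculation has been performed". It cites an audit of pilot and feasibility studies (median of 30 per arm) and adds one precision statement: "Recruitment of 60 participants in each group will allow us to measure recruitment and compliance rates with 95% CI width between 10% and 20" per cent. It gives no anticipated compliance or recruitment rate, does not say whether the width is full or half, and names no denominator.

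A separate sentence in that section covers quitting. It says of the 60 INT participants that "this is a sufficient number to estimate a proportion of patients who have quit smoking by the day of surgery", and attaches no width.

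The Primary objective defines the recruitment measure: "To establish the number of patients who agree to participate in the intervention as a proportion of those eligible to enter the study".

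Patient recruitment into study gives the targets, "60 eligible patients will be recruited to the INT group and 60 patients to the UC group", and the throughput behind them: "4000 patients a year, of whom 20% are smokers and 20% agree to take part in the study". Flow of participants during the trial explains that the UC group is made up of patients who declined the intervention and agreed to be observed.

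**The concern.** A study that tests no hypotheses is judged by how precisely it estimates the quantities it sets out to estimate. This sentence is the only precision figure in the plan, and it is unconditional. Two things do not fit.

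First, a sample of 60 gives a full 95% CI width above 20 points for most of the middle of the probability scale. A compliance rate there would be known less well than stated.

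Second, the sentence ties the precision of the recruitment rate to 60 per group. Recruitment is the primary objective and is a proportion of eligible patients. The INT participants are its numerator, and the UC participants are among those who said no. Neither group is its denominator.

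At stake is whether readers, and those planning the definitive trial, are told correctly how firm these estimates will be.

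**Working it through.** **Inputs.** n = 60 per group and the stated width of 10% to 20% (Sample size calculation). 4000 procedures a year, 20% smokers, 20% agreeing (Patient recruitment into study). About 40% of eligible preoperative patients agreeing to join smoking cessation studies (Introduction, section on the need for integrated support). The compliance rate is not given, so it is varied.

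**Formula.** Full Wald width = 2 × 1.96 × √(p(1−p)/n), treating patients as independent.

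**Step 1: can the stated range be reproduced at n = 60?** At p = 50%: 3.92 × √(0.25/60) = 25.3 points. Other rates, with two further methods:

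| Rate | Wald | Wilson | Exact |
|---|---|---|---|
| 5% or 95% | 11.0 | 12.0 | 12.9 |
| 10% or 90% | 15.2 | 15.5 | 16.7 |
| 20% or 80% | 20.2 | 20.0 | 21.5 |
| 30% or 70% | 23.2 | 22.6 | 24.4 |
| 50% | 25.3 | 24.5 | 26.4 |

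A width of 20 points requires p(1−p) = 60 × (0.20/3.92)² = 0.156, so p = 19.4% or 80.6%. A width of 10 points requires p(1−p) = 60 × (0.10/3.92)² = 0.039, so p = 4.1% or 95.9%. The stated range therefore holds only for about 4% to 19% and 81% to 96%. By the exact method it holds for 2 to 9 events in 60, or the mirror image. A full width of at most 20 points at every rate needs n = (3.92 × 0.5/0.20)² = 96.04, that is 97.

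**Step 2: other readings.**
- Half-width at n = 60: 10.1 to 12.7 points for rates of 20% to 80%. This lies inside 10 to 20, though it never comes near 20.
- Both groups pooled, n = 120: full width 10.7 to 17.9 points for rates of 10% to 90%. This also lies inside the range, but the sentence says each group.

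**Step 3: recruitment.** The denominator is the number eligible.
- 4000 × 20% = 800 smokers. This is an upper bound on those eligible, because patients must also have at least a week before surgery and be able to give exhaled CO readings. Widths: 60/800 (7.5%) 3.7; 120/800 (15%) 4.9; 160/800 (20%) 5.5 points.
- If 20% of eligible patients accept the intervention, 60 acceptors imply 60/0.20 = 300 eligible: 3.92 × √(0.20 × 0.80/300) = 9.1 points.
- If 40% accept, 60 acceptors imply 60/0.40 = 150 eligible: 3.92 × √(0.40 × 0.60/150) = 15.7 points.

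The plan's own figures thus give widths both below and inside the stated range, depending on a denominator that the sentence does not name.

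**The case against.** Much can be said for the sentence.

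- **High compliance.** If compliance is above about 81%, the stated range is correct at n = 60 (15.2 points at 90%). This stands, but the sentence sets no such condition.
- **Half-width.** A reader might infer that this reading fails too, because 20 is never reached. It does not fail: 10.1 to 12.7 lies inside 10 to 20, and an unattained upper end does not make a range false. The text does say width, however, and this reading leaves the recruitment denominator untouched.
- **Quit rates.** A reader might infer that the plan overstates the precision of quitting. The sentence names recruitment and compliance only; the quit sentence claims no width. The same arithmetic applies to any proportion within a group: at the Introduction's figure, "Only one in three smokers self-report abstinence at the time of lung cancer surgery", it gives 23.9 points. But the Introduction adds that biochemically verified rates are much lower, and from about 19% down to about 4% the width is within 10 to 20 points.
- **Recruitment.** A reader might infer that its width is certainly 4 to 6 points. The documents do not support that: 800 counts smokers before the other eligibility criteria, and at the Introduction's 40% the width is 15.7 points, inside the stated range. Nor do they show that the authors used 60 as the denominator, since none is stated. What stands is that 60 per group does not by itself fix this precision.
- **Importance.** The study tests no hypotheses, disclaims a formal calculation, also cites the audit's median of 30 per arm, and will report observed intervals in any case. This limits the harm but does not make the figure right.

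**Conclusion.** The statement is wrong as written because it is unconditional. With 60 in a group, the full 95% CI width is 10 to 20 points only for rates of about 4% to 19% or 81% to 96%. Between about 20% and 80% it is 20 to 25 points, about 5 points above the stated maximum at worst (6 by the exact method). For recruitment, defined "as a proportion of those eligible to enter the study", the width is set by the number eligible and could be anywhere from about 4 to about 16 points on figures in the protocol.

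This assumes independent patients and complete data in each group. Variation between the five centres or missing data would widen the intervals. It does not follow that 60 per group is too few, or that the primary outcome will be poorly estimated. Importance is moderate.

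**What to change.** Replace the sentence with, for example:

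*With 60 participants in a group, the 95% CI for a compliance proportion (or any other within-group proportion, such as quitting) is up to about 25 percentage points wide (full width; about 15 at 90%, 20 at 20% or 80%). The recruitment proportion is estimated among all eligible patients; its width depends on the number eligible, for example about 9 points if 60 of 300 agree and 16 if 60 of 150 agree.*

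The figure of 800 should not be presented as the number eligible, since the study itself is meant to measure that number.

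The cost is rewording and a less favourable stated precision for mid-range rates. The recruitment target and the design do not change.

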### Data analysis

Appropriate summary statistics (eg, proportions and interquartile ranges, means and SDs) will be generated for the study feasibility and patient/clinical measures. Between-group measures (mean differences) will be generated alongside 95% CI; however, formal hypothesis testing will not be carried out as the aim here is not to conclusively prove efficacy and furthermore the size of sample is too small for any inferential tests to be meaningful. Participants will be kept in the groups they were allocated, regardless of compliance with treatment (intention-to-treat protecting against attrition bias). Analysis will be completed once all participants have completed all follow-up assessments. All data used in publication will be in an anonymous format in order to maintain patient study participation confidential.

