## Trial design

### Design

Project MURRAY is an RCT comparing the effectiveness of INT verses UC in smoking cessation rates in patients undergoing major thoracic surgery, taking form of a stepped wedge cluster randomised controlled trial,^21^ and as such will not require individual patient randomisation. This feasibility study will evaluate the substantive trial and study processes.

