### Flow of participants during the trial

The anticipated pathway of patients through the trial is shown in the trial schema (figure 1). All adult patients who fulfil the inclusion and exclusion criteria during the study period will be approached and participant information sheets (PIS) will be provided. Written informed consent will be obtained after an opportunity for patients to discuss requirements for the study. If the patient accepts the intervention, they will be placed into the INT group of the study. If they decline the intervention, they will be invited to take part in the observational only part of the study and will receive UC. We will extract routinely collected preoperative and postoperative data from patient’s medical records and also collect data using questionnaires. Adverse events will be collected throughout the duration of the study. The summary of assessments is detailed in (table 1).

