### Control group of UC

As part of the feasibility study, for those patients who decline consent to receive the intervention, we ask if they would consent to be observed during the thoracic surgical pathway. Termed UC, per usual local practice, patients are typically given a leaflet about the benefits of smoking cessation and referred to their local NHS smoking cessation service, which typically last up to 12 weeks and include pharmacotherapy. Patients will also be invited for an optional telephone interview after discharge. This is to help understand smoking cessation rates in UC as well as the reasoning for non-participation in the intervention. Both groups will receive the same preoperative, perioperative and postoperative care as per protocol.

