### Protocol deviations

All study and protocol deviations will be documented in the patients case report form (CRF) and reported to the Principle Investigator, who will notify the Sponsor of any serious breaches. Patients will be analysed according to group allocation, by intent-to-treat analysis.

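### INT and UC are formed by patient choice, so the allocation and intention-to-treat wording does not fit, and the planned between-group differences with 95% CIs carry no caveat on self-selection

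*Protocol article*

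**What the plan says.** **How the groups form.** Flow of participants during the trial states: "If the patient accepts the intervention, they will be placed into the INT group of the study". It continues: "If they decline the intervention, they will be invited to take part in the observational only part of the study and will receive UC". Control group of UC agrees: "for those patients who decline consent to receive the intervention, we ask if they would consent to be observed during the thoracic surgical pathway". Patient recruitment says the same: UC is offered once a patient has turned INT down.

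**How the design is labelled.** The Design section calls Project MURRAY an RCT, "taking form of a stepped wedge cluster randomised controlled trial", with no individual randomisation. It then says that this feasibility study will evaluate the substantive trial.

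**How the data are to be analysed.** Protocol deviations states: "Patients will be analysed according to group allocation, by intent-to-treat analysis". Data analysis repeats that participants stay in their allocated groups and invokes intention-to-treat as protection against attrition bias. The same section states: "Between-group measures (mean differences) will be generated alongside 95% CI". The Abstract adds effect-size estimates with 95% CIs where appropriate.

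**How the results are to be used.** Secondary objectives include the quit proportion in each group. Control group of UC says that following decliners helps to understand quitting under usual care. Sample size calculation says the study will "inform sample size calculations for a potential larger trial".

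**The concern.** The words allocation and intention-to-treat suggest two groups that were comparable at the start. Here group membership is the patient's answer to an offer of intensive help to stop smoking, and the main clinical outcome is whether the patient stops. An answer of that kind is plausibly related to the outcome whatever INT does.

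Two results are affected. The first is the between-group difference, which would be published with a 95% CI and with no statement that the groups selected themselves. The second is the UC quit rate. In a stepped-wedge cluster trial, the control periods would contain all eligible smokers at a centre. Here UC contains only those who refused INT and then agreed to observation. Anyone planning the definitive trial from either figure would need to know this, and the article does not say it.

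**Working it through.** The article states no figure for this contrast, so there is none to reproduce. The check sets the sections side by side and then illustrates the possible size.

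**1. Is anything randomised in this study?** Flow of participants, Patient recruitment and Control group of UC give one rule: accept and enter INT, decline and be invited to UC. The article describes no randomisation of patients or centres, and no sequence, step or crossover, for the feasibility study. The allocation wording in Protocol deviations and Data analysis therefore has no allocation behind it.

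**2. What does the contrast estimate?** Write Y(INT) and Y(UC) for a patient's outcome under each form of care. The observed difference has expectation

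E[Y(INT) | accept] − E[Y(UC) | decline] = {effect of INT among acceptors} + {E[Y(UC) | accept] − E[Y(UC) | decline]}.

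The second bracket is the selection term. No acceptor is observed under usual care, so the study cannot estimate it. The 95% CI does not reflect it.

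**3. What does the UC rate estimate?** If a share w of eligible smokers accepts, the usual-care rate in all eligible smokers is w × (rate in acceptors under UC) + (1 − w) × (rate in decliners). Only the last rate is observed, and only in decliners who consent to observation.

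**4. Simple illustration.** The 60 per group is from the article. The quit rates are assumed: INT has no effect, and selection alone gives 40% v 20%.

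- SE = √(0.40 × 0.60/60 + 0.20 × 0.80/60) = √0.00667 = 0.0816
- 95% CI = 0.20 ± 1.96 × 0.0816 = 0.04 to 0.36

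**5. Range of milder and stronger selection.** Assume again that INT has no effect. Motivated patients quit at rate q between 30% and 50%, and unmotivated patients at 10%. The motivated share is a in INT and d in UC. The expected difference is D = (a − d)(q − 0.10). The chance that the 95% CI excludes zero is 1 − Φ(1.96 − D/SE) + Φ(−1.96 − D/SE).

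| Motivated share, INT v UC | D, for q from 30% to 50% | Chance CI excludes zero |
|---|---|---|
| 50% v 50% | 0 points | 5% |
| 60% v 40% | 4 to 8 points | 9% to 16% |
| 70% v 30% | 8 to 16 points | 20% to 49% |
| 80% v 20% | 12 to 24 points | 38% to 84% |

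A middle case is q = 40% with shares of 70% v 30%. The expected rates are 31% v 19%, so D = 12 points. SE = √(0.31 × 0.69/60 + 0.19 × 0.81/60) = 0.078, and the 95% CI is about −3 to 27.

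**6. Is self-selection disclosed as a limit?** The Strengths and limitations box, Objectives of the feasibility study and Data analysis all disclaim conclusions on efficacy. Where a reason is given, it is the aim of the study and the small sample. Neither is self-selection, and a larger sample would not remove the selection term in step 2.

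**The case against.** The opposing case has real substance.

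- **The contrast is already limited.** The stated aim excludes relative effectiveness, no hypothesis test is planned, and each group's quit proportion is a separate objective. The primary objective, uptake among eligible patients, is not affected. This lowers the severity. It does not supply the missing caveat, and a between-group estimate serves none of the stated objectives.
- **The RCT label may belong to the later trial.** The Design section can be read so, and Study aim supports that reading. A reader might infer that the article passes this study off as randomised. The text does not support so strong a charge, because group formation is openly described. The fault is that the two studies are not clearly separated, and that the allocation wording is applied to this study's participants.
- **Intention-to-treat is invoked against attrition bias only.** This is correct. The article does not claim that it protects against confounding, and keeping patients in the group they entered has a use. The term still presupposes an assignment that did not take place.
- **The illustration uses quit rates, whereas Data analysis names mean differences.** This is also correct, although the Abstract speaks of effect sizes more generally. The decomposition in step 2 of the working applies to a mean as much as to a proportion.
- **The direction of bias is inferred.** A reader might conclude that the difference must favour INT and that the UC rate is a lower bound. The article does not show this. Decliners are typically referred to NHS services that include pharmacotherapy. Eligibility counts anyone who smoked in the last 28 days, so some decliners may already have stopped.
- **The use in planning is not spelt out.** A reader might infer that the decliner rate or the INT–UC difference is meant to feed the next sample size, and that the definitive trial would be too small by some multiple. Sample size calculation attaches that purpose to the 60 INT patients. It names neither figure as an input. Any multiple would also need a true control rate and a true effect, and the article gives neither.

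**Conclusion.** The point stands and should be fixed. The groups are patient-chosen, the wording on allocation and intention-to-treat does not describe them, and differences with 95% CIs are planned without any caveat on self-selection. The UC quit rate is a rate among consenting decliners.

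The size is unknown. Under the assumptions above (no INT effect, 60 per group), selection alone could produce anything from a 4-point difference, whose CI would usually include zero, to 20 points or more with a CI that excludes zero. All these quit rates and motivated shares are assumed. That acceptors and decliners differ in motivation is plausible but unmeasured. The documents do not support a statement that the bias certainly favours INT, or that the definitive trial will be undersized by a given factor.

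**What to change.** 1. In Design, state that the stepped-wedge cluster RCT is the substantive trial and that this feasibility study is non-randomised with patient-chosen groups. In Protocol deviations and Data analysis, replace the allocation and intention-to-treat wording with a statement that patients are analysed in the group entered at consent.
2. In Data analysis and the Abstract, report each group separately with a 95% CI and drop the between-group differences. If they are kept, label them explicitly as non-causal and subject to self-selection. Adjustment for baseline Fagerstrom score, exhaled CO and smoking history, which Table 1 lists for both groups, is optional. None of these measures motivation directly, so adjustment would not remove confounding by it and should not be presented as doing so.
3. In Secondary objectives and Control group of UC, label the UC quit rate as a decliner rate. In Sample size calculation, state that neither this rate nor the INT–UC difference will by itself be taken as the control rate or effect size when the definitive trial is planned.

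The cost is wording only, with no new data or patients. If the contrast is dropped, the study loses an INT-versus-UC figure that could not be interpreted causally.
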